**Arm 1: Blood or plasma donation**
Blood or plasma donationParticipants with perfluorooctane sulfonate >5 ng/mL were prioritized for this arm
Blood: 12-month commitment to donating blood every 12 weeks. Each blood donation will take approximately an hour to an hour and 15 minutes each time.Plasma: 12-month commitment to donating plasma every 6 weeks. Each plasma donation will take approximately an hour and 30 minutes to 2 hours each time.Additional surveys administered will involve a time commitment between 30 to 45 minutes.Blood or plasma control group12-month commitment into the control groupAdditional surveys administered will involve a time commitment between 30 to 45 minutes.
**Arm 2: Zone 2 physical activity**
Zone 2 physical activity intervention4-month commitment to completing a minimum of 45 minutes of physical activity in zone 2 for a minimum of 4 days per week.
Cardiopulmonary Exercise Test (CPET) testing before beginning and after completing the zone 2 arm for 4 months.
4-month commitment to wear a wrist-worn heart and health tracker at all times unless it is charging.Additional surveys administered will involve a time commitment between 30 to 45 minutes.Zone 2 control group4-month commitment to wear a wrist-worn heart and health tracker at all times unless it is chargingCPET testing before beginning and after completing the participation in zone 2 control group arm for 4 months.Additional surveys administered will involve a time commitment between 30 to 45 minutes.
**Arm 3: Intermittent fasting**
Intermittent fasting intervention4-month commitment. The participant will limit intake of food and calorie-containing beverages to an 8-10 hour window a day and fast for the remaining 14-16 hours on 4 days per week.Additional surveys administered will involve a time commitment between 30 to 45 minutes.Intermittent fasting control group4 month-commitment into the control groupAdditional surveys administered will involve a time commitment between 30 to 45 minutes.

#### Data Management

Research activities primarily occur through electronic communications such as email, text, and internet-based surveys, telephone contacts, or postal or express mail. Surveys are self-administered by participants on a computer or smartphone. Should participants be unable or unwilling to access them online, they may be administered by study staff by telephone. Participant information given to study staff via phone or email conversation is entered and stored in the REDCap database [25].

The database for this study is maintained through REDCap, which securely keeps participant identifiers and contact information according to the University of Arizona’s standard operating procedures. These procedures operate with respect to cybersecurity, privacy, patient confidentiality, and compliance with applicable patient privacy regulations. All study-related documents and specimens contain a unique identifier for each participant, with any study-related documents with personal identifiers stored in a locked cabinet in lockable offices on campus. Laboratory results are entered directly into the REDCap study database from the study reference laboratory.

Twilio is a cloud-based communications platform that allows for automated text messaging chains to be sent to study participants. It is used to send study survey links to their phones that will take them directly to secure REDCap surveys.

At enrollment and their end-of-study visit, all participants provide biological specimens (blood and urine), and a survey is administered to collect information on occupational history and exposures, relevant medical history, sleep quality, physical activity information, a food frequency questionnaire, the Center for Epidemiological Studies Depression scale (short form), and environmental exposures (Table 1, and described further in the Outcomes section). Throughout their enrollment period, all participants also receive regular study adherence questionnaires (described below). At end-of-study only, all participants additionally take a cognitive assessment (MindCrowd, described below). Participants assigned to the zone 2 physical activity arm complete a CPET before the beginning of the 4-month intervention and again after the conclusion of the intervention. Once participants in the zone 2 physical activity arm report the results of their first CPET, they are sent a wrist-worn accelerometer (Garmin Forerunner 45) that they are instructed to wear throughout the 4-month period and to return upon completion.

Zone 2 wears their accelerometer every day for the duration of the trial.

**Table 1 table1:** Participant data collection time points for participants enrolled in the firefighter collaborative research project.

	Baseline	Mid-intervention	End of study^a^
Blood	All	BP^b^	All
Urine	All	BP	All
Questionnaires^c^	All	BP	All
Adherence^d^	N/A^e^	All^f^	N/A
Cardiopulmonary Exercise Test	Z2^g^	N/A	Z2
MindCrowd cognitive assessment (verbal cognition, processing speed)	N/A	N/A	All
Accelerometer	Z2	Z2	Z2
Epigenetics (Infinium MethylationEPIC v2.0 BeadChip)	All	N/A	All
VO2max, resting heart rate, HRV^h^, HR^i^ recovery	Z2	Z2	Z2
Sleep quality (accelerometer): deep, REM^j^, light	Z2	Z2	Z2
Sleep quality (National Health Interview Survey Questionnaire): hours, rested, interruptions	All	N/A	All
Depression (CES-D^k^ Short form)	All	N/A	All
Firefighter gear and occupational exposures	All	N/A	All
Dietary quality	All	N/A	All
Self-reported weight	All	All	All

^a^End of the study is approximately 4 months after randomization for zone 2 and intermittent fasting and approximately one year for blood or plasma.

^b^BP: blood/plasma arm.

^c^Questionnaires include diet, depression or mood, physical activity, occupational characteristics, and lifestyle.

^d^Intervention adherence questionnaires are evaluated weekly for IF and Z2, and monthly for blood or plasma.

^e^N/A: not applicable.

^f^All: all arms.

^g^Z2: Zone 2 physical activity.

^h^HRV: heart rate variability.

^i^HR: heart rate.

^j^REM: rapid eye movement.

^k^CES-D: Center for Epidemiologic Studies Depression Scale.

#### Biological Specimens

All participants provide up to 50 mL of blood via venipuncture at baseline as part of the study screening process and at the completion of assigned study arm activities. Participants in the blood and plasma arm complete an additional collection at mid-study, between 4 and 8 months. Each venipuncture is performed by qualified study staff, phlebotomists, nurses, or paramedic-EMTs at organized study events hosted at participating fire stations or facilities. Upon collection, blood specimens are stored locally in coolers with ice packs for transportation to the University of Arizona, where they are processed within 24 hours, with aliquots stored at –80 °C before testing. Baseline blood specimens for all participants are analyzed for PFAS as the final step in the study screening process and for markers of epigenetic age, such as DNA methylation patterns. At the end of assigned activities, only participants in the blood and plasma arm will have their blood specimens analyzed for PFAS. All blood specimens collected at the end of assigned activities for all study arms will be analyzed for markers of epigenetic age.

Participants are asked to self-collect approximately 80 mL of urine at baseline as part of the study screening process and at the completion of assigned study arm activities per FFCCS protocol and to be stored for future analyses. Participants in the blood and plasma arms complete an additional collection at mid-study, between 4 and 8 months. Collections take place at organized study events hosted at participating fire stations or facilities. Upon collection, urine specimens are locally stored on dry ice for transportation to the University of Arizona, where specific gravity is measured using the Atago Refractometer (Model PAL-10S, Cat# 4410, Fisher Scientific). The sample is aliquoted and prepared for long-term storage at –80 °C for potential future analyses associated with these interventions.

#### Adherence to Study Activities and Retention

To determine activity adherence, participants are contacted at regular intervals determined by their intervention via email or secure SMS test messages using Twilio. Each survey asks if the participant has completed their required study activities. Participants randomized to an intervention are asked detailed questions about completing their activities, and participants randomized to control are asked if they engaged in the intervention activities since the last study survey. During the check-in surveys, participants are able to report any adverse events. They will then be contacted by study coordinators, and the events will be reported to the IRB for review to determine any necessary actions to take.

Study coordinators call and email noncompliant participants each week to improve adherence. Participants are contacted if they are due to start study activities but have not completed their baseline survey, have at least 1 week past due for a blood or plasma donation, have not completed a weekly survey for zone 2 physical activity or intermittent fasting in 2 weeks, or have not scheduled an appointment for a follow-up biological collection. Participants may also be contacted if they do not sync their wrist-worn accelerometer (Garmin Forerunner 45) with their mobile application, or if they do not share the results of their CPET with the study team. If the participant does not respond and continues to fall behind on study activities, then the IRB-approved liaison for their department is contacted to engage with the participant and ensure they complete their activities.

### Laboratory Methods

#### Per- and Poly-Fluoroalkyl Substances Concentrations

Serum samples are tested for PFAS by the New Jersey Department of Health Centers for Disease Control method #6304.09 as a reference using Chronos online SPE – uHPLC by Spark Holland coupled with a Sciex 7500 MS/MS. A total of 20 analytes are tested, including perfluorobutanesulfonic acid, perfluorodecanoic acid, perfluoroheptanesulfonic acid, perfluoroheptanoic acid, perfluorohexanesulfonic acid, perfluorohexanoic acid, perfluorononanoic acid, perfluorooctanesulfonamide, perfluoroundecanoic acid, PFOA (perfluorooctanoic acid), PFOS, branched and linear isomers of PFOA and PFOS, 9-Chlorohexadecafluoro-3-oxanonane- 1-sulfonic acid, 4,8-Dioxa-3H-perfluorononanoic acid, 2-(N-Ethyl-perfluorooctane sulfonamido) acetic acid, 2-(N-Methyl-perfluorooctane sulfonamido acetic acid), and Hexafluoropropylene oxide dimer acid. Note that total PFOA and total PFOS are calculated as the sum of the branched and linear isomers [26].

#### DNA Methylation Analysis

DNA methylation analysis of serum samples is conducted at the University of Arizona Genetics Core. After sample accessioning and preparation, genomic DNA is extracted using a Qiagen DNeasy Blood and Tissue Kit (REF: 69581) or similar following the manufacturer’s recommendations for whole blood. The extracted DNA is then quantified using promega quantiflor fluorometric dsDNA assay (PN: E2671) and dsDNA quantities are detected using a SynergyHT plate reader (Agilent or Biotek). Samples are then normalized or diluted robotically with HPLC water to the range of 200-500ng in a total volume of 45uL. Following normalization, a bisulfite conversion using the Zymo EZ-96 DNA Methylation Kit (PN: D5004) is performed with the specified thermocycler conditions (95 °C for 30 sec, 50 °C for 60 min for 16 cycles, and Hold” at 4 °C) with 15uL as the final elution volume.

The bisulfite-converted DNA is then input into the illumina infinium methylation EPIC Kit (PM 20087706-8) following the manufacturer’s recommendations. Whole genome amplification is then performed on the bisulfite-converted DNA. The amplified DNA is then fragmented and precipitated before being resuspended and hybridized onto the bead chip (v2.0) during an overnight incubation. Unhybridized DNA is washed off before the bead chip undergoes single base extension and staining. Before scanning, the bead chip undergoes a final round of washing and coating to prepare the chip for imaging. Once prepped for imaging, the bead chip is then scanned on an Illumina NextSeq 550 following the manufacturer’s recommendations.

Depression and mood are evaluated at baseline and follow-up using the revised version of the Center for Epidemiologic Studies Depression Scale. Diet quality is measured from a food frequency questionnaire at baseline and follow-up. Sleep quality is measured via the wrist-worn accelerometers for those in the zone 2 arm, and through a modified version of the Centers for Disease Control’s National Health Interview Survey’s Sleep Surveillance questionnaire for all participants. The National Health Interview Survey sleep survey is slightly modified to account for firefighter’s shift work.

### Statistical Considerations

#### Power Analysis

We conducted a power analysis based on the outcomes of changes in PFAS concentrations, as well as changes in epigenetic ages. Following the initial Australian study, to see a change in concentration of 20% PFOS from before and after, we calculated an N of approximately 100 participants per group or 300 total for the blood, plasma, or control groups. However, to observe a change of one year of epigenetic age acceleration, with a standard deviation of 3, we required an N of 141 per group. To account for missingness, we are targeting an N of 150 per group.

Therefore, the targeted sample size for PFOS ≥5 ng/mL is 150 plasma test participants, 150 blood test participants, and 150 shared controls for blood or plasma; and for PFOS <5 ng/mL we are targeting 75 intervention participants; for zone 2 is 150 controls and 150 test participants; for intermittent fasting, sample size is 150 controls and 150 test participants. Thus, the total number of participants that complete the study is targeted at 1120. Randomization of the intervention groups is conducted using R v4.2.0 [34].

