## Results

This study was funded by the Arizona Board of Regents. Enrollment began in August 2023 and concluded in November 2024. As of January 2025, a total of 916 participants were enrolled in the study and 1893 participants were screened. The conclusion of the blood and plasma interventions is set for December 2025, contingent upon funding. Data analysis will begin once sufficient data has been collected.

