### Limitations

Our study has some limitations; first, there are significant barriers to plasma donation, including time commitment and distance, which can impede participant adherence. The Australian study being replicated identified an adherence rate of 93.7% to their interventions [11]. All the intervention arms require a time commitment; therefore, compliance is a concern [35]. Finally, not meeting enrollment targets will reduce our study's power to evaluate relationships between the intervention and PFAS levels and epigenetic age acceleration.

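### Enrolment closed at 916, too few for the required 141 in every main group; the stated target (1120, listed groups sum to 1125) is ambiguous and the shortfall is not acknowledged

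*Protocol article*

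**What the plan says.** In the Protocol article, the Power Analysis section gives two sizings. The PFOS outcome needs about 100 per group. The epigenetic outcome is sized "to observe a change of one year of epigenetic age acceleration, with a standard deviation of 3", for which "we required an N of 141 per group". The section continues: "To account for missingness, we are targeting an N of 150 per group".

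It then lists the targets:
- 150 plasma, 150 blood and 150 shared controls at PFOS 5 ng/mL or above
- 75 intervention participants below 5 ng/mL
- 150 and 150 for zone 2
- 150 and 150 for intermittent fasting

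The section concludes: "Thus, the total number of participants that complete the study is targeted at 1120".

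The Results section reports: "Enrollment began in August 2023 and concluded in November 2024". It adds: "As of January 2025, a total of 916 participants were enrolled in the study and 1893 participants were screened".

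Limitations says that "not meeting enrollment targets will reduce our" power for the PFAS and epigenetic-age relationships. It does not say that the targets were missed, and it gives no figure.

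**The concern.** Epigenetic age acceleration is the primary outcome shared by all arms, and its sizing sets the 150 per group. Three statements do not fit together.

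- The total differs from the sum of its parts.
- A number already raised for missingness is described as the number who complete.
- Enrolment has closed well below either version of the target, while the text still presents 141 to 150 per group as the basis and the shortfall as something that might happen.

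A reader who judges a null epigenetic result against the Power Analysis section would credit the trial with a size that it cannot have in every group.

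**Working it through.** **Inputs.** From Power Analysis: difference 1 year, SD 3, 141 per group, raised to 150, the group list, and the total of 1120. From Results: enrolment closed, 916 enrolled. From the Interventions section: each participant is randomised to one arm, as intervention or control, so nobody counts twice. The section gives no alpha, sidedness or power; these are inferred in step 1.

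**1. Reproduce 141.** n = 2(z_α + z_β)² SD²/Δ². With two-sided 0.05 and 80% power: 2 × (1.96 + 0.8416)² × 9 / 1 = 141.3, which matches the stated 141 (142 if rounded up). The other standard choices do not match: one-sided 0.05 gives 112 at 80% power and 155 at 90%, and two-sided 0.05 at 90% gives 190.

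**2. Missingness allowance.** 1 − 141/150 = 6.0%.

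**3. Total.** 7 × 150 + 75 = 1125. The stated 1120 is 5 short (0.4%), with no effect on power.

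**4. What the total counts.**
- If 150 is an enrolment number, the matching figure after loss is 7 × 141 = 987, plus 70.5 to 75 for the PFOS <5 group. The range depends on whether the same 6% applies to that group, whose 75 is not derived. The sum is about 1058 to 1062.
- If 1125 is the completer number, enrolment at 6% loss would have to be 1125/0.94 ≈ 1197.
- 916 is below all of these.

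**5. Shortfall without assuming a split.** Seven main groups at 141 need 987, and 916 < 987. Even with nobody in the PFOS <5 group, the average is 916/7 = 131. With that group at its 75, it is (916 − 75)/7 = 120. So at least one main group is below 141 before any loss. Overall, 916/1125 = 81%.

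**6. Size under a proportional split (assumption).** A 150-target group holds 150 × 916/1125 = 122. Power = Φ(Δ/(SD√(2/n)) − 1.96). Detectable difference at 80% power = 2.8016 × 3 × √(2/n).

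| Case | n per group | Power for 1 year | Detectable difference (years) |
|---|---|---|---|
| Plan | 141 | 80% | 1.00 |
| 916, no loss | 122 | 74% | 1.08 |
| 916, 6% loss | 115 | 71% | 1.11 |
| 916, 10% loss | 110 | 70% | 1.13 |

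The 6% is the plan's own implied allowance. The 10% is illustrative: in Data Analysis it is the level of missing data that triggers a multiple-imputation sensitivity analysis, not an expected attrition rate.

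**The case against.** **The shortfall is visible.** The article prints the target, the closure and the 916, and Limitations says that missed targets reduce power for both outcomes. This stands in part. What is lacking is the comparison, a statement that the target was missed, and the consequence.

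**A completer target of about 1120 could be coherent.** The allowance is for missingness, which completers can also have, and the Abstract speaks of enrolling up to 1500. (Overall Study Design calls 1500 a screening goal.) This stands as far as it goes: the total should not be relabelled as enrolment on our authority. It supports asking for clarification, and 916 falls short on either reading.

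**A reader might infer that no group has 141 participants.** The documents do not support that. Counts per group are not given, and an even spread is doubtful. Donation was opened to five further states while zone 2 and fasting stayed in Arizona, and Textbox 2 says that participants with higher PFOS were prioritised for donation. Some groups may have reached 141, and others may be well below 120.

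**A reader might also infer that the PFAS comparison is underpowered.** That is not shown either. It needs about 100 per group, and 122, 115 and 110 all exceed that under a proportional split. The actual donation group sizes cannot be checked.

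**A protocol should record the planned basis.** Agreed. Achieved figures belong beside the 141/150 statement and should not replace it.

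**Conclusion.** The concern holds for the epigenetic-age sizing. It is certain, given one arm per participant, that 916 enrolled cannot supply 141 in each of the seven main groups, and that the text does not acknowledge this. It is also certain that the listed targets sum to 1125, and that the section leaves unclear whether its total counts people enrolled or people completing.

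The loss is moderate: about 70% to 74% power for 1 year instead of 80%, or a detectable difference of 1.08 to 1.13 years instead of 1.00. These figures assume two-sided 0.05, SD 3, a split proportional to the targets and losses of 0% to 10%. Of these, only the SD is stated. The certain part needs none of them. The addition error alone would be a copy-edit.

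**What to change.** 1. Correct the total to 1125. State whether it is an enrolment or a completer target, and make it consistent with the step from 141 to 150.
2. Keep the planned basis (1 year, SD 3, 141 raised to 150), and state the alpha, sidedness and power behind it.
3. Beside it, give the number randomised in each group at closure, with the resulting power or detectable difference for each epigenetic-age contrast at a stated loss.
4. In Limitations, replace the conditional sentence with the actual shortfall: 916 of 1125, or 81%. Say that it bears on the epigenetic-age sizing, and report whether the donation groups still meet the roughly 100 per group needed for PFOS.

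The cost is restated figures, using counts that the study team should already hold. Neither conduct nor analysis changes. The downside is a less favourable stated power.

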#### Data Analysis

All models will evaluate intent to treat effects, as well as the average treatment effect of the treatment. We will first evaluate characteristics by treatment group to ensure randomization is effective.

To estimate the effect of blood and plasma donation on the reduction of PFAS concentration, mixed effects models with random effects by department or region will be fit to compare changes in PFAS concentration before and after the study among intervention groups. We will report mean differences in the change from baseline to end-of-study measurements by group and adjust for residual confounders. We will also evaluate whether the volume of plasma and blood donated is a significant predictor of PFAS change, and account for adherence in these models. The results of these models will evaluate if there is a statistically significant difference in the change of PFAS concentration from baseline to follow-up, in cases compared to controls, and if there is a dose-response relationship between volume donated and PFAS concentration change.

Linear mixed-effect models will also be used to examine differences between groups in epigenetic age acceleration, cardiovascular fitness, cognitive functioning (measured only at follow-up), mental health, sleep quality, and other measured outcomes. Similar models will be used for zone 2 physical activity and intermittent fasting interventions. Missing data will be assessed and if substantial missing data is identified (greater than 10%), a sensitivity analysis will be conducted using multiple imputations by chained equations.

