In the human body, PFAS accumulates primarily in the liver, kidneys, and blood. Long-chain PFAS, such as perfluoro octane sulfonate (PFOS) and perfluorooctanoic acid (PFOA), have reported half-lives of several years (3.1-7.4 and 2.1-8.5, respectively) [8]. These chemicals bind strongly to albumin, the most abundant protein in plasma [8,10]. Therefore, these chemicals may be removed from the body through blood or plasma donation. An Australian study among firefighters previously demonstrated the effectiveness of blood or plasma donation to lower serum PFAS levels over 12 months, although no health effects were investigated. Findings from the study revealed that plasma donation was more effective than blood donation at reducing the mean serum level of PFOS at 12 months, while serum PFOS did not significantly change in the control group [11]. Plasma donation reduced PFOS levels by approximately 24% (–2.9 ng/mL, 95% CI –3.6 to –2.3 ng/mL), while blood donation reduced PFOS levels by approximately 11% (–1.1 ng/mL, 95% CI –1.5 to –0.7 ng/mL) [11]. Based on the findings from that study and concern for PFAS exposure, Arizona firefighters requested research to replicate the study and additionally investigate health outcomes such as cardiovascular health and epigenetic age acceleration.

Lifestyle and environmental exposures are associated with DNA methylation patterns, a type of epigenetic alteration. DNA methylation affects gene expression by adding a methyl group to 5’—C—phosphate—G—3’ dinucleotides. These DNA methylation patterns can be analyzed to determine epigenetic age or “biological age” through epigenetic clocks. Previous research has found that accelerated epigenetic age can be a risk factor for cancer, cardiovascular and neurological diseases, as well as death from all causes combined [12]. In addition to the physical health impacts, accelerated epigenetic age has been linked to negative mental health impacts [13]. Studies on firefighters have found differential DNA methylation patterns, or accelerated epigenetic age, potentially as a result of fire ground exposure and increased serum PFAS levels [7,14].

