#### Interventions

Randomization groups are created at regular monthly intervals and clustered by recruitment region. Participants who have consented to participate in the study are randomized into 1 of the 4 study arms as either an intervention or control, accounting for their eligibility determined during the screening process and baseline serum PFOS concentrations. Upon enrollment into their specific group, participants are provided with instructional materials for assigned activities, activity timelines, and frequently asked questions.

Participants randomized in the blood donation or plasma donation arm include all participants with serum PFOS ≥5 ng/mL, following the previous Australian study [11], while also meeting additional study criteria outlined in Textbox 1. We also included a smaller intervention group of participants with PFOS <5 ng/mL in the plasma arm, to evaluate whether improvements in epigenetic age are independent of baseline PFOS. Participants in the blood intervention arm are expected to donate whole blood every 12 weeks for 12 months, while those in the plasma intervention are expected to donate plasma every 6 weeks for 12 months. Participants are provided with a list of donation centers in their region and acceptable types of donations (eg, whole blood donation is acceptable, but not “Power Red” or platelets). Participants go to donation centers on their own. Controls are asked to refrain from donating plasma or blood throughout the trial period.

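### Entering adherence in the PFAS models would stop the group coefficient being the randomised effect and would strip most of the precision from a within-group volume slope

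*Protocol article*

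**What the plan says.** In the protocol article, Data Analysis opens with "All models will evaluate intent to treat effects, as well as the average treatment effect of the treatment". It then plans mixed models for the change in PFAS by group. It adds that the team will test whether "the volume of plasma and blood donated is a significant predictor of PFAS change, and account for adherence in these models". The closing sentence of that paragraph gives these models two jobs: to compare the change between intervention and control participants, and to show "if there is a dose-response relationship between volume donated and PFAS concentration change". The section extends similar models to the zone 2 and fasting arms.

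Other sections fix what the two variables are. Under Interventions, the schedule reads "donate whole blood every 12 weeks for 12 months, while those in the plasma intervention are expected to donate plasma every 6 weeks for 12", the last figure being in months. Under Adherence to Study Activities and Retention, "Each survey asks if the participant has completed their required study activities", which for donors means donations made. By contrast, "participants randomized to control are asked if they engaged in the intervention activities since the last study survey", so an adherent control is one who did not donate. Power Analysis sets the groups at "150 plasma test participants, 150 blood test participants, and 150 shared controls for blood or plasma".

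**The concern.** Adherence is an outcome of assignment, not a baseline characteristic. Once it sits beside assigned group, the group coefficient compares groups at a chosen level of adherence, and adherence means opposite behaviours in donors and controls. The result is not the randomised contrast.

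In the volume model the difficulty is overlap. For a donor, volume is close to adherence × scheduled donations × volume per donation. Holding adherence fixed within a donation group leaves mainly the variation in volume per donation, so most of the information on dose is lost. A flat slope could then be reported as absence of a dose-response when the model had little chance of finding one.

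Leaving adherence out does not make the slope causal. Participants largely decide how much they donate, so the volume slope may also carry health, access and motivation. The Limitations section names compliance as a concern, so adherence is likely to vary enough for this choice to matter.

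**Working it through.** **The plan's own figure.** The article gives none for the dose-response model. The group size used below, 141, is its figure for epigenetic age: n = 2(1.960 + 0.842)² × 3² / 1² = 141.28, which reproduces it (two-sided 5% and 80% power assumed).

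**Inputs for the main check.** From the documents: about 8 plasma donations (52/6 = 8.7, taken as 8) and a 24% PFOS fall, the plasma result quoted from the Australian study. Assumed: 700 mL per donation (SD 60 mL), donations drawn as Bin(8, logit⁻¹(1.4 + u)) with mean adherence 76%, residual SD 0.20 on log PFOS change, and an unmeasured confounder u with effect −0.03 per SD. There were 1,000 simulated trials with 141 per group.

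**Step 1: true effect per litre and intent-to-treat effect.**
- Full-adherence volume = 8 × 0.7 = 5.6 L
- Slope = ln(0.76)/5.6 = −0.274/5.6 = −0.049 per litre
- Intent-to-treat effect = −0.049 × 5.6 × 0.76 = −0.21

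**Step 2: add adherence beside assigned group.** With adherence as a fraction, its coefficient is set by the donors: the volume-only slope of about −0.065 per litre × 5.6 L = −0.364 per unit. The group coefficient is then the intent-to-treat effect minus −0.364 × (mean adherence in donors − value given to controls).
- Controls coded 0: −0.21 + 0.364 × 0.76 = +0.07 (simulation +0.08, SE 0.07)
- Controls coded 1: −0.21 − 0.364 × 0.24 = −0.30 (simulation −0.30, SE 0.03)

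With no confounder the same arithmetic gives 0 and −0.27. If mean adherence were 93.7%, the rate the article quotes from the Australian study, the intent-to-treat effect would be −0.274 × 0.937 = −0.26, and the two codings would still give 0 and −0.27. High adherence therefore brings the second coding close to the randomised effect but does not rescue the first.

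**Step 3: volume slope among donors.**
- Volume only: about −0.065 per litre, against the true −0.049, with power above 99%.
- Volume plus adherence: about −0.049, with SD 0.046 across trials. The variance inflation factor is 11, so the correlation is √(1 − 1/11) = 0.95. The ratio 0.049/0.046 = 1.07 implies power near 19%, and the simulation agrees.
- Assignment as instrument: −0.21/(5.6 × 0.76) = −0.049.

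**Step 4: how far the precision loss depends on the model.** This second simulation used 150 per group, 300 runs and no confounding. Assumed: 0.47 L per blood donation, 0.80 L per plasma donation, adherence near 80%, true slope −0.40 and residual SD 2. Ranges run over a coefficient of variation (CV) of volume per donation of 5%, 10% and 20%.

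| Data and model | Slope variance multiplied by | Power without → with adherence |
|---|---|---|
| Plasma group alone (correlation 0.98 / 0.94 / 0.80) | 31 / 8.7 / 2.9 | 0.91→0.10 / 0.94→0.28 / 0.98→0.74 |
| Blood and plasma, group term | 3.5 / 2.9 / 1.9 | 0.95→0.49 / 0.96→0.59 / 0.98→0.88 |
| Blood and plasma, no group term (correlation about 0.4) | 1.2 | 1.00→1.00 |
| All three groups, no group term | 1.0 to 2.2 | 1.00→1.00 |

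Adjusted slopes averaged about −0.40. The exception was the noisiest setting (plasma alone, CV 5%), at −0.295 with SE 0.655. I read that as simulation noise, because an irrelevant regressor does not bias a correctly specified linear slope. With a shared cause of adherence and PFAS change added, the unadjusted within-group slope was about −0.48 to −0.53 and the adjusted one about −0.40 to −0.45.

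If volume is recorded as donations × a fixed nominal volume, volume and adherence are exactly collinear within a group and the slope is not identified there.

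**The case against.** The strongest reply is that the text says to account for adherence, which could mean weighting, restriction or an instrument, and that such detail may sit in an analysis plan not shown here. Intent-to-treat analysis is promised at the outset, and the volume analysis is introduced as an addition. This stands in part. The omission of detail is no fault in an article. But accounting for a variable in a model ordinarily means a term in it, and the next sentence gives the same models the group comparison, with nothing to keep adherence out.

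Four stronger readings are tempting and are not supported:
- *The adjustment biases the dose-response.* In the check it does not. The volume-only slope is the biased one, and the adjusted slope is nearer the truth but too imprecise to use.
- *The adjustment removes the treatment effect.* That needs controls coded as non-adherent, whereas the adherence section suggests a compliant control counts as adherent. Even so, −0.30 is not the randomised effect either.
- *Blood and plasma litres are summed on one scale, against the rationale that* "These chemicals bind strongly to albumin, the most abundant protein in plasma". The article names both volumes but never says they are added.
- *No randomisation-based estimate of treatment received is planned.* The article names a treatment-effect estimand without its estimator, so an instrument may be intended. One can say only that none is stated.

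**Conclusion.** The concern holds in limited form. As ordinarily read, the sentence puts a post-randomisation variable into models that also deliver the group comparison, and sets it beside a volume variable that it nearly duplicates within a donation group.

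The first fault changes the meaning of the group coefficient: −0.21 becomes +0.08 or −0.30 according to a coding choice alone. The second costs precision: power falls from over 99% to about 20% in the main set-up, from 0.91–0.98 to 0.10–0.74 for plasma alone in the second, and hardly at all if groups are pooled without a group term. Confounding of the volume slope by self-selected dose is a separate matter and exists with or without this sentence.

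All magnitudes rest on assumed adherence, volume per donation, residual SD and confounder strength. In particular, the adjusted slope escapes confounding only because volume per donation was simulated as unrelated to the confounder. An intent-to-treat comparison fitted without adherence is unaffected. This should be changed before analysis, but it does not undermine the trial.

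**What to change.** Amend the Data Analysis wording, or settle it in the analysis plan, as follows:

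1. State that adherence is not a term in the randomised intent-to-treat comparison of PFAS change.
2. Estimate the effect of donation received with randomised assignment as instrument for volume donated, separately for plasma versus the shared control and for blood versus the shared control.
3. Do not enter adherence beside volume within a donation group or in a model with a group term.
4. Report the within-donor volume slope by donation type, adjusted for baseline variables only, and label it exploratory and observational.
5. Apply the first rule to the similar models for the zone 2 and fasting arms.

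The cost is wording and one extra model. The per-litre estimate will have a wider interval than the naive regression. It also relies on the exclusion restriction, that assignment affects PFAS only through donation. The Results section says analysis starts only once sufficient data have been collected, so the change can be made without reference to outcomes.
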